**Author : [name]**

### **1.1 Background**

Malaysia has made a commitment at the 69th World Health Assembly to eliminate hepatitis as major public health threat by 2030 (Ministry of Health [MOH], 2020). To achieve this, 90% infected individuals with hepatitis C need to be diagnosed and 80% hepatitis C infected individual that eligible for treatment will need to be started on treatment by 2030 (WHO, 2017). To show this commitment, Malaysia have taken the initiative to scaled up hepatitis C treatment by making the generic version of DAA available in Malaysia and by launching the Malaysian National strategic plan for hepatitis B and C in 2019. However, it was estimated that in Malaysia, 90% from 380 000 chronic hepatitis C individuals were still undiagnosed and untreated (Mohamed et al., 2019). In addition, the 2018 “Baseline estimates for WHO’s 10 core indicators for the Global Reporting System for Hepatitis” have reported that, only 6.1% of hepatitis C patient knew their status and 1.4% were started on treatment. Thus, Malaysia is still far from reaching the targets for hepatitis C elimination set by the WHO.

Malaysia were still in the process of expanding the hepatitis C treatment, the generic DAA regimes were only available at selected MOH facilities where limited numbers of patients will be treated in stages (Mohamed et al., 2019). Currently, it was estimate that treatment were only available for around 23000 patient (Mohamed et al., 2019). MMT clients is one of the most important target populations for upscaling hepatitis C screening and treatment. Hepatitis C infections were found to be highly prevalence among MMT clients in Malaysia. The Malaysia methadone treatment outcome study has reported that 64.6% of their respondent among MMT clients were diagnosed with hepatitis C (Ali et al., 2018). In addition, a third of death among MMT clients were found to be related to hepatitis C infection (Ali et al., 2018). Even with the availability of DAA which has high cure rates and more tolerable, it was observed that the awareness and knowledge regarding hepatitis C and the fact that its curable were still very low among MMT clients (Mukherjee et al., 2017 ; Chan et al., 2022). Chan et al., (2022) in their study which is a part of interim review of the Malaysia strategic plan for hepatitis C further highlight that the reason for hepatitis C treatment were not

widely accepted among people living with hepatitis C was found due to limited disease awareness and disease related stigma. Furthermore, a negative attitude towards hepatitis C treatment could further influence hepatitis C treatment uptake among this population (Yang & Tang, 2000). In addition, some studies have found that more than 40% of MMT clients in their research still engage with illicit drug use along with MMT treatment (L. Li et al., 2012; White et al., 2014). Thus, MMT clients can be considered a pool of individuals at high risk of developing hepatitis C infection due to their history of drug use and current risk of relapse into drug addiction. Moreover, some healthcare workers involved in hepatitis C care on MMT clients find it difficult to convince clients for hepatitis C screening and treatment which reflect the low treatment coverage of 1.4% reported in 2018 (Mukherjee et al., 2017 ; MOH, 2020 ; Chan et al., 2022). This reflects that the willingness of MMT clients to receive hepatitis C treatment upon diagnosis was still low and the need for a program or module to prepare them and increase their willingness for treatment as the government scaled up the hepatitis C treatment in Malaysia.

Currently, there are no comprehensive hepatitis C health education programs in Malaysia to deliver information regarding the advancement in hepatitis C diagnosis and treatment to MMT clients. Furthermore, not much study has been done to investigate the effectiveness of theory-based health education intervention in increasing the willingness for hepatitis C treatment among MMT clients. Hence this study offers to evaluate and add to the body of knowledge on the effectiveness of theory-based health education intervention in increasing MMT client willingness for hepatitis C treatment.

## **1.2 Objectives**

### **1.2.1 General Objectives**

The general objectives of this study are to develop, implement and evaluate the effectiveness of Theory of planned behaviour-based hepatitis C health education intervention module in improving willingness for hepatitis C treatment among MMT clients in Malacca.

### **1.2.2 Specific Objectives**

The specific objectives of this study are:

- i. To develop and implement a Theory of planned behaviour-based hepatitis C education intervention module to increase willingness to hepatitis C treatment.
- ii. To identify the sociodemographic characteristics, MMT treatment profile, HIV and hepatitis C status, alcohol use, drug history and history of attending hepatitis C educational program of the respondents in the intervention and control group at baseline.
- iii. To evaluate the effectiveness of Theory of planned behaviour-based hepatitis C education intervention module in improving willingness for hepatitis C treatment among MMT clients in Malacca.
  - i. Within intervention group and within control group from baseline to immediately post-intervention and 3 months post-intervention.
  - ii. Between groups (intervention group and control group) at baseline, immediately post-intervention, and 3 months post-intervention.
  - iii. Within and between groups over time.
- iv. To evaluate the effectiveness of Theory of planned behaviour-based hepatitis C education intervention module in improving knowledge, attitude towards

behaviour, subjective norms, and perceived behavioural control for hepatitis C treatment among MMT clients in Malacca.

- i. Within intervention group and within control group from baseline to immediately post-intervention and 3 months post-intervention.
- ii. Between groups (intervention group and control group) at baseline, immediately post-intervention, and 3 months post-intervention.
- iii. Within and between groups over times.

### **1.3 Research Hypotheses**

The research hypotheses of this study are:

**H1-** There is higher willingness for hepatitis C treatment within group and between group in intervention group compared to the control group at immediate and 3 months post-intervention.

**H2-** There is higher knowledge for hepatitis C within group and between group in intervention group compared to the control group at immediate and 3 months post-intervention.

**H3-** There is higher positive attitude towards hepatitis C infection within group and between group in intervention group compared to the control group at immediate and 3 months post-intervention.

**H4-** There is higher positive hepatitis C related subjective norms within group and between group in intervention group compared to the control group at immediate and 3 months post-intervention.

**H5-** There is higher hepatitis C related perceived behavioural control within group and between group in intervention group compared to the control group at immediate and 3 months post-intervention.

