**Table 3.1. Information for sample size calculation**

| Study Characteristic | Assumption made by investigator                                                                                                                        |
|----------------------|--------------------------------------------------------------------------------------------------------------------------------------------------------|
| Type of study        | Randomize Control Trial                                                                                                                                |
| $Z_{(1-\alpha/2)}$   | $Z_{(1-\alpha/2)} = 1.96$ , the value of the standard normal distribution corresponding to a significance level of alpha of 0.05 for a two-sided test. |
| $Z_{(1-\beta)}$      | $Z_{(1-\beta)} = 0.842$ , the value of the standard normal distribution corresponding to the desired level of power of 80%.                            |
| $P_1$                | $P_1 = 0.75$ , Proportion of respondent willing for treatment in intervention group at 3 months post intervention                                      |
| $P_2$                | $P_2 = 0.44$ , Proportion of respondent willing for treatment in control group at 3 months post intervention                                           |
| $\bar{P}$            | $\bar{P} = (0.75 + 0.44) / 2$ , $\bar{P} = 0.595$                                                                                                      |

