### **1.14 Study Variables**

#### **1.14.1 Dependent Variables**

##### **1) Primary outcome**

The primary outcome of this study will measure the willingness of the clients for hepatitis C treatment following diagnosis of hepatitis C

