### **1.15 Data Analysis**

#### **1.15.1 Statistical Test in Data Analysis**

Data collected will be analysed using IBM SPSS (Version 27.0). Data exploration will be performed to look for any error in data entry, missing data and presence of outliers.

The distribution of numerical data will then be determined whether they are normally or not-normally distributed. In determining the normality of data both statistical and graphical method will be use. For statistical method, the Skewness/SE of skewness and the Kolmogorov-Smirnov parameter will be calculated, while for the graphical method, the histogram together with stem and leaf box plot will be plotted and analyses. Furthermore, after determining the normality of data, mean and standard deviation will use to described normally distributed data, while median with first and third quartile (Q1, Q3) will be used to described not normally distributed data. Categorical data will be presented as frequency and percentage.

For between group comparison, the independent sample t-test will be used to compare the mean different of continuous and normally distributed data between intervention and control group. For continuous but not normally distributed data, the Mann-Whitney U test will be used to compare between intervention and control group. The Chi-square test will be used to compare frequency different of categorical data between intervention and control groups and for data of 2 by 2 table that contains cell with an expected count less than 5 for more than 20%, the Fisher's exact test will be use.

For within group changes overtime comparison, the One-way repeated measure ANOVA will be used for continuous and normally distributed variables. Within group analysis for categorical data will use the Cochran's Q test.

The Generalized Linear Mixed Model (GLMM) will be used to test the main effect and interaction between and within the intervention and control groups overtime (baseline, immediately post intervention, and 3-month post intervention). This study will use a significance level with a *p*-value of 0.05 and a confidence interval of 95% for hypothesis testing. For results yielded *p*-value of less than 0.05 will be consider as statistically significant findings.

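### H1 and objective iii count within-arm change, two visits and several tests as evidence of effectiveness on willingness with no decision rule, while the trial is sized only for the between-arm difference at 3 months

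*Protocol*

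**What the plan says.** Four parts of the protocol bear on what would show that the module works on willingness.

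- **Hypothesis (1.3).** H1 expects "higher willingness for hepatitis C treatment within group and between group in intervention group compared to the control group at immediate and 3 months" post-intervention. One sentence holds two kinds of comparison and two time points. H2 to H5 follow the same pattern.
- **Objective (1.2.2, iii).** Effectiveness on willingness is to be evaluated in three ways. The first is "Within intervention group and within control group from baseline to immediately post-intervention and 3 months post-intervention". The second is "Between groups (intervention group and control group) at baseline, immediately post-intervention, and 3 months post-intervention". The third is within and between groups over time.
- **Outcome (1.14.1).** "The primary outcome of this study will measure the willingness of the clients for hepatitis C treatment following diagnosis of hepatitis C". No time point or contrast is attached.
- **Analysis (1.15.1).** For the yes/no outcome, the between-arm test is chi-square (Fisher's exact for sparse tables). Within arms, "Within group analysis for categorical data will use the Cochran's Q test". A GLMM is also used "to test the main effect and interaction between and within the intervention and control groups overtime". Results with a p-value "of less than 0.05 will be consider as statistically significant findings". None of these tests is named as primary.

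The sample size section and Table 3.1 are narrower. P1 is the "Proportion of respondent willing for treatment in intervention group at 3 months post intervention", 0.75, and P2 is the same quantity in controls, 0.44, with two-sided alpha 0.05 and 80% power. That is one between-arm comparison at one visit.

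**The concern.** The protocol sizes one comparison but lists several as evaluations of effectiveness, and gives no rule for combining them. The reader cannot tell whether H1 is met when one of them is significant, when all are, or only when the sized one is. Each reading gives the trial different operating characteristics, and none is shown to match the stated 5% and 80%.

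The within-arm route matters most. A rise in the intervention arm alone does not show that the module worked, because controls may rise too, for instance through repeated questioning or the national expansion of treatment described in 1.1. Yet objective iii lists that change as an evaluation of effectiveness. At stake is whether a general rise in willingness, or a difference seen only immediately after the session, could be reported as success on the primary outcome.

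**Working it through.** **1. Reproduce the sizing.** Inputs from Table 3.1: P1 = 0.75, P2 = 0.44, mean 0.595, z-values 1.96 and 0.842.

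n = {1.96·√[2(0.595)(0.405)] + 0.842·√[0.1875 + 0.2464]}² / 0.31²
= {1.96(0.6942) + 0.842(0.6587)}² / 0.0961
= (1.9153)² / 0.0961 = 38.17, so 39 per arm.

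The stated 39 reproduces from the general formula. (The printed substitution line, with 1.19(1 − 0.405), would give 50.5; this does not affect the present point.) Power at exactly 39 per arm is 80.9%. The 39 therefore supports one two-sided 0.05 test between arms at 3 months, and only that.

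**2. Reading A: any one significant result may support the claim.** Two independent tests at 0.05 give 1 − 0.95² = 9.75%. Five give 1 − 0.95⁵ = 22.6%, an upper figure because the tests here are correlated.

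For the correlated case, three binary visits were simulated. Assumptions:

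- 44% willing at every visit in both arms
- latent correlation between visits 0.3 to 0.8
- 39 per arm (the pre-dropout figure) and 118 per arm (the recruited figure)
- Wald tests standing in for the GLMM group effect and the group-by-time interaction
- no clustering

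The five tests are chi-square at T1, chi-square at T2, the group effect, the interaction, and Cochran's Q in the intervention arm.

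| Rule | Two-sided rejection | Favourable direction only |
|---|---|---|
| One test at T2 (as sized) | 5% | 2.5% |
| T1 or T2 | about 9-10% | about 4-6% |
| Any of five | about 16-18% | about 8-10% |

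**3. The within-arm route when both arms rise.** Same set-up, but both arms go from 44% to 54% at T1 and T2, so the arms do not differ. Cochran's Q in the intervention arm is significant in:

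- about 15-27% of trials at 39 per arm
- about 41-70% of trials at 118 per arm

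The higher figures go with the stronger correlation.

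**4. Reading B: both T1 and T2 must be significant between arms.** Assume 0.75 v 0.44 at both visits, which the protocol states only for 3 months. At 39 per arm:

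- independent tests: 0.809² = 65%
- lower bound: 2(0.809) − 1 = 62%
- upper bound (fully dependent): 81%

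This reading does not inflate the type I error, but power generally falls short of the planned 80%.

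**5. After naming one test.** With the T2 between-arm difference as the sole primary test, alpha stays at 0.05 and n at 39 per arm before dropout. Keeping T1 and T2 as alternatives at 0.025 each would need 47 per arm; 39 would give 71.8% power.

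**The case against.** H1 is joined by *and*, and no sentence says that either visit or any single test is enough. Read literally, all parts must hold, which does not inflate the error rate. That stands: a reader might infer that the protocol permits success on any one result, but it does not print such a rule. What remains is that it prints no rule at all, lists the comparisons separately under effectiveness, and calls every p below 0.05 significant.

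H1 also says *higher* and names a comparator. So the two-sided rates should not be read as the chance of wrongly declaring the module effective; the favourable-direction column is the relevant one. It is smaller, though still above 2.5%. Likewise, a significant Cochran's Q after a real rise correctly rejects its own null, and the control arm's change is to be reported beside it. It misleads only if taken as evidence of effectiveness, which objective iii invites.

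Two further inferences are not supported:

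- A GLMM main effect averaged over visits that include baseline would understate a post-intervention effect. That costs power; it does not create false positives.
- The simple tests do not establish a contradiction with intention to treat. A chi-square at one visit omits only those missing that visit, and 1.15.2 leaves the missing-data method open.

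Finally, the link function and baseline adjustment may properly sit in an SAP, and the intended contrast can be guessed from Table 3.1. But the hypothesis and objective are stated here, and an SAP naming one test would have to override them.

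**Conclusion.** The point holds as a badly fixed primary hypothesis. The 3-month between-arm difference, the only quantity sized, is not singled out in H1, objective iii, the outcome definition or the analysis section, and within-arm change is given standing as evidence of effectiveness.

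The size depends on the reading. Under an any-result rule, which is an assumption, the favourable false-positive rate is roughly two to four times the nominal 2.5%. Under an all-must-hold rule the error rate is safe, but joint power is about 65% if the tests are independent. The within-arm figures rest on an assumed 10-point rise from 44% and assumed correlations, and the GLMM tests were approximated, so all simulated rates are indicative. The mismatch itself needs no simulation: it is visible by setting 1.3 and 1.2.2 beside Table 3.1.

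This should be corrected, because it determines what the trial can conclude and costs little.

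**What to change.** - In 1.14.1 and 1.15.1, name one primary test: the between-arm difference in willingness at 3 months (T2), estimated as the arm contrast at T2 from the GLMM already planned, at two-sided 0.05.
- Make the T1 comparison and the knowledge, attitude, subjective norm and perceived control outcomes secondary.
- Make the within-arm tests and the baseline between-arm comparison descriptive.
- Remove the within-group wording from H1 to H5, and remove within-arm change from the objectives that evaluate effectiveness.

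This changes protocol wording only. The visits, data, model and 39 per arm before dropout (as far as this point is concerned) stay the same. The price is that a result at T1 or within the intervention arm can no longer support the primary claim.

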## **METHODOLOGY**

### **1.4 Study Location**

This study will be conducted in Malacca which is one of the states in Malaysia.

### **1.5 Study Duration**

This study will commence October 2022 August 2024.

### **1.6 Study Design**

This study is a two-armed, parallel, single blinded, cluster randomized controlled trial (CRCT).

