#### 1.7.5 Sampling Unit

The sampling unit will be individual who is active MMT clients of government health clinics in Malacca.

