#### Sampling Method

The list of MMT clients based on the registration number were screen for eligibility criteria. Those who does not fulfil the eligibility criteria will be remove from the list. Subsequently, the cleaned registration number list will be arranged in ascending order. Following that each client will be assigned number starting from number one to total number of the population. In the next step simple random sampling will be conducted using online random number generator from <https://stattrek.com/statistics/random-number-generator.aspx> website to recruit participant according to number of sample size required.

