#### 1.7.6 Sample Size Estimation

The sample size calculation for this study was calculated based on the primary outcome desire which is willingness for hepatitis C treatment. The sample size calculation will be calculated using the formula for testing the different in proportion between two groups (Lwanga et al., 1991). The formula and calculation are as depicted below:

$$n = \frac{\{[Z_{(1-\alpha/2)} * \sqrt{2\bar{P}(1-\bar{P})}] + [Z_{(1-\beta)} * \sqrt{P_1(1-P_1) + P_2(1-P_2)}]\}^2}{(P_1-P_2)^2}$$

$$n = \frac{\{[1.96 * \sqrt{1.19(1-0.405)}] + [0.842 * \sqrt{0.1875 + 0.2464}]\}^2}{(0.31)^2}$$

$$n = 39$$

Thus, the sample size calculated is equal to 39 for one arm. Total sample size for both control and intervention groups are 78 persons (39 x 2). Following that, an additional adjustment for dropouts were made based on the 77% attrition rate from previous study (Arain et al., 2016). Therefore, the adjustment for response rate is 78/(1-L) (L= attrition rate) = 78/0.33= 236 (118 respondents per arm) (KK Gupta et al., 2016). Thus, the sample size needed for this study is 118 pairs of intervention and control groups which amount to 236 subjects. The information used for sample size calculation is as

presented in Table 3.1. The calculation was based on findings from a randomize control trial study for willingness of hepatitis C treatment (Arain et al., 2016).

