## 1.8 Randomisation

### 1.8.1 Sequence Generation

Upon recruiting the participant who fulfil the eligibility criteria according to sample size calculated, random allocation sequence will be generated to allocate respondents into either intervention or control groups. Randomization sequence will be generated using software from web page “Create a block randomization list” (Sealed Envelope Ltd, 2019) .

In this study, the permuted block randomization will be used to allocate respondent into either the intervention or control group. This permuted block randomization will be conducted using the software from web page “Create a block randomization list” (Sealed Envelope Ltd, 2019). The flow chart of study design will be presented by adopting the CONSORT 2010 flow diagram in the result section after conducting the study as presented in Figure 3.2 (Moher et al., 2010).

[figure not shown]

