**Figure 3.2. Flow Chart of Study Design and Outcome Evaluation**

### 1.8.2 Allocation Concealment

In this study, the allocation concealment method that will be use is the “sequentially numbered, opaque, sealed enveloped methods” as depicted in Figure 3.3. In the process of randomization and allocation concealment, a randomization list will be generated using software from web page “Create a block randomization list” (Sealed Envelope Ltd, 2019). The list will also include unique allocation codes generated by the software which consist of two letters followed by 1 or more digits (E.g: BW2, AM4, AB1 and etc). This unique code will represent either the intervention or the control group and meaning of the code will only be known by the sequence generator. This will ensure concealment of the allocation. Following that, the “sequentially numbered, opaque, sealed enveloped methods” will be use during respondent recruitment. The unique code will be print out, cut out and sealed in opaque envelops. Subsequently, as patient were being recruited, the opaque enveloped containing the different code will be pulled out by liaison officer at each clinic. The randomisation code will only be release after patient have been recruited into the study which take place after the baseline measurement have been completed. By doing this, the parties involve during the randomization process will be blind from the group that the respondent will be allocate

[figure not shown]

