### **1.13 Data collection process**

At the start of the study, clients were randomly selected from the sampling frame and allocated into intervention and control groups. A liaison officer was appointed from each clinic with selected participants and was trained on the study procedures. Eligible clients were approached for consent, and baseline data were collected from those who agreed to participate.

Participants in the intervention group received an intervention package within one to two weeks. The session lasted approximately 30 minutes and included a health talk on hepatitis C and a video featuring a patient sharing their experience with DAA treatment. Outcomes were assessed immediately after the intervention (T1) and again three months later (T2). The control group completed the same assessments at baseline, one to two weeks after baseline (T1), and three months after T1 (T2). After the final assessment, the same intervention package was provided to the control group.

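### Section 1.6 declares a cluster randomised trial, but sampling, sample size and allocation all describe randomisation of individual clients

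*Protocol*

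**What the plan says.** Section 1.6 (Study Design) is one sentence: "This study is a two-armed, parallel, single blinded, cluster randomized controlled trial (CRCT".

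The operational sections describe something else:

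- Section 1.7.5 (Sampling Unit): "The sampling unit will be individual who is active MMT clients of government health clinics in Malacca".
- Sampling Method: one cleaned list of client registration numbers, then "In the next step simple random sampling will be conducted using online random number generator". There is no stage at which clinics are drawn.
- Section 1.7.6 (Sample Size Estimation) uses the "formula for testing the different in proportion between two groups". Table 3.1 gives the type of study as a randomised controlled trial, without the word cluster. Neither place mentions an ICC, a cluster size, a number of clinics or a design effect.
- Section 1.8.1 (Sequence Generation): "the permuted block randomization will be used to allocate respondent into either the intervention or control group".
- Section 1.8.2 (Allocation Concealment): as patients are recruited, "the opaque enveloped containing the different code will be pulled out by liaison officer at each clinic", and a patient's code is released only after baseline measurement.
- Section 1.13 (Data collection process): "clients were randomly selected from the sampling frame and allocated into intervention and control groups".

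Section 1.15.1 names t-test, Mann-Whitney, chi-square or Fisher tests between groups, and a generalised linear mixed model (GLMM) for group, time and their interaction.

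**The concern.** The unit of randomisation is a basic design fact. It decides which sample size formula applies, which tests are valid and what readers expect to see reported. It belongs in the protocol, so it cannot be left to a separate analysis plan, and here it is stated in two incompatible ways.

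If section 1.6 is right, the sampling and allocation procedures are wrong, the sample size lacks a design effect, and the between-group tests treat correlated respondents as independent. If the procedures are right, the label is wrong. An ethics reviewer, reader or meta-analyst would then look for a cluster count, an ICC and a cluster-adjusted analysis that do not exist.

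**Working it through.** **1. Which unit is randomised?** In a cluster trial all participants of a clinic share an arm. Section 1.8.2 has an officer at each clinic draw an envelope for each patient after that patient's baseline, so both arms can occur in one clinic. Sections 1.7.5, 1.8.1 and 1.13 and the Sampling Method agree with that. No section defines, counts or allocates clusters. Only section 1.6 points to clusters.

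**2. Which design does the sample size belong to?** Inputs from Table 3.1: P1 = 0.75, P2 = 0.44, mean P = 0.595, z = 1.96 and 0.842. The formula is that of section 1.7.6.

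- First term: 1.96 × √(2 × 0.595 × 0.405) = 1.96 × 0.6942 = 1.3607
- Second term: 0.842 × √(0.1875 + 0.2464) = 0.842 × 0.6587 = 0.5546
- n = (1.3607 + 0.5546)² / 0.31² = 3.668 / 0.0961 = 38.17, rounded up to 39 per arm

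This is the protocol's figure, reached with no clustering term. (The printed substitution shows 1 − 0.405 where 0.405 is needed; as printed it would give 50.5. That is a separate slip.)

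Power at n per arm is Φ[(0.31√n − 1.3607) / 0.6587]. At n = 39 it is 80.9%. The stated 39 is therefore the sample size of an individually randomised trial.

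**3. What if clinics really were randomised?** The protocol gives neither the number of clinics k nor the ICC, so both are assumed here: k from 6 to 20, ICC from 0.01 to 0.05. Take the 78 evaluable clients that section 1.7.6 plans for, with m = 78/k per clinic and design effect DE = 1 + (m − 1) × ICC. Power is the formula above at 39/DE. The number needed is 38.17 × DE, rounded up.

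| k | m | ICC | DE | 39/DE | Power | Needed per arm |
|---|---|---|---|---|---|---|
| 20 | 3.9 | 0.01 | 1.029 | 37.9 | 80% | 40 |
| 20 | 3.9 | 0.05 | 1.145 | 34.1 | 75% | 44 |
| 6 | 13 | 0.01 | 1.12 | 34.8 | 76% | 43 |
| 6 | 13 | 0.05 | 1.60 | 24.4 | 60% | 62 |

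A normal approximation is generous when clinics are few, so true power at the small-k end would be lower still.

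**4. What if individuals are randomised and clinic is ignored?** This was simulated under no intervention effect: 236 clients, blocks of 4 handed out regardless of clinic, 6 or 20 clinics, ICC 0.01, 0.05 and 0.20, 10,000 runs each. The unadjusted two-proportion test rejected in 4.95% to 5.4% of runs against a nominal 5%. Allocation is independent of clinic, so clinic differences do not materially inflate the error rate.

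**The case against.** The strongest reply is that this is a labelling error. All the procedures agree on individual randomisation, the 39 per arm is correct for that design, and the individual-level tests are valid for it. On that reading one sentence changes and neither the sample size nor the inference moves. This stands, and it sets the limits of the point. It does not remove the contradiction, because nothing in the protocol says that section 1.6 is the part to disregard.

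A reader might infer more than the documents support:

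- *That ignoring clinic spoils the error bars under either design.* Step 4 shows otherwise for individual randomisation. Chance imbalance between clinics is already covered by the p-value. Officers who deliver the session to several intervention clients could add some clustering within that arm. This has not been quantified, and the simulation does not cover it.
- *That one unstratified block list is shared across clinics.* Sections 1.8.1 and 1.8.2 give neither the number of lists nor any strata. Envelopes drawn by an officer at each clinic would also fit one set per clinic.
- *That the analysis leaves clinic out.* Section 1.15.1 names no clinic term, but the random effects of a GLMM are commonly set in an analysis plan, and that plan is not at hand.
- *That power is far below the 60% to 80% range.* Combining clustering with the 77% attrition in section 1.7.6 gives lower figures. But 236 × 0.23 is about 54 completers, for whom power is already about 65% with no clustering. Most of that loss comes from the attrition arithmetic, which is a separate matter. A design effect computed on all 236 enrolled would likewise not match a power calculation based on 78 completers.

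**Conclusion.** The design statement in section 1.6 contradicts sections 1.7.5, 1.7.6, 1.8.1, 1.8.2 and 1.13 and the Sampling Method, and must be reconciled with them. The weight of the text favours individual randomisation. On that reading the error is confined to the label: 39 evaluable per arm stands and the individual-level tests are valid.

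There is a numerical consequence only if clinics are to be randomised. Power with 78 completers would then be about 60% to 80%, and 40 to 62 evaluable per arm would be needed in place of 39. Those ranges rest entirely on the assumed 6 to 20 clinics and ICC of 0.01 to 0.05. At an ICC of 0.01 the loss is small (76% to 80%).

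**What to change.** **Needed.** Reword section 1.6 to *two-arm, parallel, individually randomised controlled trial*, keeping the blinding statement. This costs one sentence and leaves the 39 evaluable per arm and the individual-level tests unchanged.

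**Advisable, for balance and precision.** State in sections 1.8.1 and 1.8.2 that the permuted-block list is stratified by clinic, with one sequentially numbered envelope set per clinic, and include clinic in the GLMM (a random intercept, or a fixed stratum if clinics are few). The reason is that one medical officer per clinic collects the data and delivers the session (sections 1.10.1 and 1.11.2.4). The cost is a stratified list, one model term and slightly more envelope preparation.

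**Only if clinics are really to be randomised.** Rewrite sections 1.7 and 1.8 around clinics, replace the individual-level between-group tests with a cluster-level or mixed-model analysis, and restate the power with an explicit ICC and number of clinics. This is a redesign, and it would probably need more participants.
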